### Recruitment and data collection

The patients who fulfill the study inclusion criteria will be recruited consecutively by their therapists at the beginning of their inpatient treatment in the four cooperating psychotherapeutic inpatient units (St. Franziska-Stift Bad Kreuznach, MediClin Seepark Klinik Bad Bodenteich, Segeberger Kliniken Gruppe Bad Segeberg and Luisenlinik Bad Dürreheim). Prior to participation, the patients will be informed with oral and written information regarding the study by their therapists. After written informed consent is obtained, the patients will be randomly assigned to the IG or the CG.

#### Randomization

The patients will be randomized using a stratified block randomization with randomly varying block size to ensure concealment and equal group sizes, and the randomization will be stratified by the participating clinical units. The randomization will take place at the individual level at the University Medical Center Hamburg-Eppendorf one week before the beginning of the intervention. The allocation schedule was created with a computer program (Microsoft Excel, Windows) by a researcher at the University Medical Center Hamburg-Eppendorf. The therapists will be informed about the randomization outcome prior to the last psychotherapeutic session during inpatient treatment so that they can inform the patients about their group assignment before discharge.

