## Abstract

**Background:** Depressive and anxiety disorders are highly prevalent, but only a small percentage (approximately 50%) of patients receive appropriate treatment. Relevant barriers include communication and coordination gaps between different providers that result from the lack of integration between different care-giving systems. Aftercare following inpatient treatment represents one of these gaps because systematic follow-up care does not exist. Case management-based aftercare coordination by phone might be a promising approach to overcoming this gap and improving long-term treatment outcomes. Case management is a patient-centered and situation-based approach comprising systematic tracking and support of patients by a case manager. The aim of this study is to evaluate the effectiveness of aftercare coordination by phone for patients with depressive and anxiety disorders.

**Methods/design:** The effectiveness of aftercare coordination will be investigated in a prospective randomized controlled trial in four psychotherapeutic inpatient routine care units (St. Franziska-Stift Bad Kreuznach, MediClin Seepark Klinik Bad Bodenteich, Segeberger Kliniken Gruppe Bad Segeberg and Luisenklinik Bad Dürkheim). The patients receiving aftercare coordination (intervention group; IG) will be compared with those who receive treatment as usual (TAU control group; CG). Eligible patients will be required to have a diagnosis of an anxiety and/or depressive disorder and a recommendation for follow-up outpatient psychotherapy.

The aftercare coordination consists of six phone contacts at intervals of two weeks that are performed by therapists in the inpatient units. The patients will complete questionnaires at discharge ( $t_1$ ), 3 months after discharge (i.e., at the end of the intervention ( $t_2$ )) and 9 months after discharge ( $t_3$ ). The primary outcome will be change in symptom severity from  $t_1$  to  $t_3$ , the secondary outcomes will be health-related quality of life and the proportion of patients who manage to begin outpatient psychotherapy by  $t_3$ .

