### Methods/design

#### Study design

The study will be performed as prospective multicenter randomized controlled trial (Figure 1). The patients who receive aftercare coordination by phone (IG) will be compared to those who receive TAU without aftercare coordination by phone (CG). Measurements will be performed at three time points in each group. Baseline measures will be taken at discharge from the inpatient treatment (which will be the beginning of the intervention;  $t_1$ ), and two follow-up measures will be taken after 3 months at the end of the intervention ( $t_2$ ) and again 6 months after the end of the intervention (which will be 9 months after discharge from inpatient treatment;  $t_3$ ).

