### Statistical analyses

The primary analysis will focus on the changes in symptom severity from  $t_1$  to  $t_3$  as assessed with the BDI-II. Comparisons between the IG and the CG will be calculated with mixed model analyses of covariance (ANCOVAs) with symptom severity as the dependent variable and gender and initial symptom severity as covariates. An advantage of this method is that it includes all available data even if the data from another time point for a specific person are missing. Other secondary analyses will be performed regarding changes in health-related quality of life, self-efficacy and anxiety symptom severity from  $t_1$  to  $t_2$  and from  $t_1$  to  $t_3$ . Following the intention-to-treat approach (ITT), we will analyze all randomized participants in the primary analysis to avoid biases such as non-random attrition of the participants. Additionally, a sensitivity analysis following the per-protocol approach will be conducted. This analysis will be performed including only the participants that have completed all measurements. To investigate whether the patient characteristics (e.g., age, level of education, and psychosocial treatment before the inpatient treatment) and patient ratings of the therapeutic alliance predict the outcomes

of the aftercare coordination, different regression analysis models will be applied to the primary and secondary outcomes. Process evaluation and data about the patients' satisfaction and acceptance will be investigated via descriptive and qualitative analyses. We will also conduct drop-out analyses to compare the demographic and clinical baseline characteristics of the completers and non-completers ( $t$ - and  $\chi^2$ -tests). The analyses will be conducted with SPSS 21.

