#### Power calculation

We expect a moderate effect size, which is defined as  $f = 0.25$  according to Cohen [35], for the primary outcome because recent studies that have investigated aftercare programs have reported moderate effect sizes in terms of changes in symptom severity (e.g., depressiveness) [36]. We expect a reduction of the error variance of approximately 30% due to the inclusion of initial symptom severity (BDI at  $t_1$ ) as a covariate (which can be expected to be uncorrelated with the study conditions due to the randomization). These considerations lead to an adjusted effect size of  $f = 0.29$ . To detect a moderate effect between the intervention and control groups in terms of the symptom severity with a power of 80% and an  $\alpha$  of 0.05, a sample size of  $N = 96$  (48 per group) is required. Based on an expected dropout rate of approximately 50% from baseline ( $t_1$ ) to 9 months of follow-up ( $t_3$ ), we aim to include a sample of  $N = 192$  (96 per group) to perform the per-protocol analysis with a sufficient sample size.

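### The protocol does not ensure that the t1 baseline BDI-II is completed before the allocation is disclosed, although t1 is the starting point and covariate of the primary analysis

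*Protocol*

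**What the plan says.** Four parts of the protocol bear on this.

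- **Order of allocation and disclosure (Randomization).** Patients are randomized centrally "one week before the beginning of the intervention". On disclosure, "The therapists will be informed about the randomization outcome prior to the last psychotherapeutic session during inpatient treatment", and the stated purpose is "so that they can inform the patients about their group assignment before discharge".
- **Timing and mode of t1 (Study design; Abstract).** "Baseline measures will be taken at discharge from the inpatient treatment", a point that the same sentence equates with the start of the intervention. The Abstract confirms self-report: "The patients will complete questionnaires at discharge".
- **Use of t1 (Statistical analyses).** "The primary analysis will focus on the changes in symptom severity from" t1 to t3 on the BDI-II, using mixed-model ANCOVAs "with symptom severity as the dependent variable and gender and initial symptom severity as covariates".
- **Premise about t1 (Power calculation).** The t1 BDI is expected to cut the error variance by about 30%, and it is described as a covariate "which can be expected to be uncorrelated with the study conditions due to the randomization".

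No section places the t1 questionnaire before disclosure, and none plans a BDI-II at admission or before randomization to serve as baseline.

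**The concern.** Randomization makes a covariate independent of study arm if the covariate is fixed before allocation, or if knowing the allocation cannot change it. The protocol secures neither condition for t1. Patients are not blinded, the BDI-II is self-rated, and the news is not neutral. One group hears that its own therapist will phone six times over 12 weeks. The other hears that it will have no further contact with that therapist. A patient who already knows this when filling in t1 may score differently because of it.

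Any such shift would enter the primary result, because the primary model adjusts the t3 comparison for t1. Part of a difference at t1 that was created by disclosure would be treated as a pre-existing imbalance and corrected for. The correction would be wrong by an amount that depends on the t1–t3 correlation.

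**Working it through.** **1. Order of events.** Allocation is generated one week before the intervention begins, and the intervention begins at discharge (t1). The therapist knows the result before the last session, and the patient is to know before discharge. t1 is taken at discharge. As written, disclosure may precede t1, and nothing prevents it.

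**2. The plan's own figures.** For a two-group F-test with f = 0.29, two-sided alpha 0.05 and 80% power, the required N is 95.3, rounded up to 96 (48 per group). Power at N = 96 is 80.3%. Dividing by 1 − 0.50 for dropout gives 192. Both stated figures reproduce, and the sample size is not in question here.

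**3. Inputs for the illustration.**
- From Power calculation: f = 0.25, so d = 2 × 0.25 = 0.50; error-variance reduction 30%; 48 per group.
- Implied t1–t3 correlation: r = √0.30 = 0.548.
- Assumed, not in the protocol: a between-arm t1 shift s of 0.05 to 0.3 SD caused by disclosure, equal SDs at t1 and t3, and at first no carry-over to t3. The gender covariate is ignored.

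**4. Formula.** With equal SDs the ANCOVA slope is r, so a spurious t1 difference s moves the adjusted t3 difference by r × s. The standard error in SD units is √0.70 × √(2/48) = 0.171.

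| Shift s (SD) | Bias r × s (SD) | Share of d = 0.50 | Two-sided type I error | Power if bias is toward no effect |
|---|---|---|---|---|
| 0 | 0 | 0% | 5.0% | 83% |
| 0.05 | 0.03 | 5% | 5.3% | 79% |
| 0.1 | 0.05 | 11% | 6.2% | 74% |
| 0.2 | 0.11 | 22% | 9.8% | 63% |
| 0.3 | 0.16 | 33% | 16.1% | 50% |

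A simulation at s = 0.2 gave a bias of 0.109 SD, against 0.110 from the formula. The starting power is 83% and not 80% because a full 30% reduction gives f = 0.25/√0.70 = 0.299, and a normal approximation was used. The plan's f = 0.29 corresponds to a reduction of about 26%.

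**5. Direction.** If intervention patients report fewer symptoms than controls at t1 because of the news, the bias works against the intervention. The opposite shift inflates the effect.

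**6. Carry-over.** If a fraction c of the shift persists to t3, the bias relative to the effect of the phone contacts themselves is (r − c) × s. It vanishes at c of about 0.55 and changes sign above that.

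**7. Leaving t1 out.** With no carry-over, comparing t3 between arms without t1 as covariate is free of this bias. The effect size is then f = 0.25. Power at N = 96 is about 68%, and 80% power needs N = 127.5, rounded up to 128.

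**The case against.** The strongest reply is that the protocol gives no sequence within the discharge period. Its wording allows the therapist to inform the patient but does not say that t1 follows. Some patients may complete t1 first. Figure 1 was not readable in the text available, so an order shown only there could not be checked. This stands: a reader might infer that t1 is always taken after disclosure, and the document does not say so. What remains is that nothing secures the safe order.

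Three further objections also stand.

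- **Reparability.** A reader might infer that no later analysis could deal with the problem. With no carry-over, a t3-only comparison does, at the cost in power shown above.
- **Change scores.** A reader might apply the full shift s, which would be 20% to 60% of d for shifts of 0.1 to 0.3 SD. That describes an unadjusted change score. The protocol specifies adjustment for t1, and with t1 in the model, change and t3 as dependent variable give the same arm effect. Only r × s applies.
- **Reach.** The alliance questionnaire might seem equally exposed, but the protocol does not state when it is given. Nor does it say that the content of the last session differs by arm.

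It is also fair that the shifts are assumptions, that a 0.3 SD shift from hearing the allocation would be 60% of the effect planned for the whole intervention, and that relief in the intervention group or disappointment among controls would bias against the intervention. None of this removes the gap, because a bias route in either direction weakens the primary estimate.

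Finally, the remark that t1 is uncorrelated with arm serves to justify the variance reduction, and the sample size reproduces. That is correct, but the same premise supports using t1 as a covariate in the primary model.

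**Conclusion.** The point holds as a gap in the order of procedures, not as a demonstrated bias. The protocol allows the allocation to be known before t1 is completed, uses t1 in the primary model, and relies on an independence from study arm that its schedule does not protect. A statistical analysis plan could not repair the order in which the data were collected.

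The size and direction of any effect cannot be derived from the document. Under the stated assumptions (shift of 0.05 to 0.3 SD, no carry-over, r = 0.55, equal SDs) the adjusted difference is biased by about 0.03 to 0.16 SD, or 5% to 33% of d = 0.50. At the lower end this is minor. The bias is smaller or reversed if the shift persists to t3. The documents do not support reading this as a certain bias, as one beyond any repair, or as an error in N = 96 or N = 192.

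**What to change.** In the Study design and Randomization sections, require the t1 questionnaire to be completed and logged before the allocation is released to therapist and patient, and record the dates of t1 completion and of disclosure. Randomization can stay where it is in the schedule, provided the result is withheld until t1 is logged.

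The cost is modest. t1 may fall slightly before the day of discharge, so its definition needs a small change of wording. The coordinating centre must confirm receipt of t1 before releasing the result, which is a small logistic step at each unit. The sample size, the arms and the intervention do not change.

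Where t1 has already been collected without this safeguard, a comparison of t3 without t1 as covariate can serve as a sensitivity analysis, with the loss of power stated.

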#### Description of the intervention and control conditions

##### Intervention condition

The aftercare coordination is based on the concept of case management, which is a patient-centered approach that aims to support the patient in finding and organizing his or her individual aftercare treatment. After the inpatient treatment, the patients in the intervention group will receive six aftercare coordination phone contacts at intervals of two weeks that will be performed by their inpatient treatment therapists for 12 weeks. The task of the therapists will be to accompany and guide the patients in matters related to making plans and generating goals. The patients should

[figure not shown]

**Figure 1** Study design and expected sample sizes.

be motivated and encouraged in terms of empowerment to become active in organizing their own aftercare treatment, and the therapists will provide feedback by monitoring the steps taken toward goal achievement. During the aftercare coordination, and in contrast to therapeutic interventions, the treatment of the patients' disorder-specific complaints will not be the primary focus. The main contents of the phone contacts will be the patients' needs and problems associated with their aftercare coordination and supportive consultation from the therapist.

Prior to initiating the aftercare coordination, the therapists will be trained in their role as a coordinator and receive an elaborate manual that will provide guidelines for the phone contacts. This detailed manual contains helpful instructions for the therapist but allows sufficient freedom to tailor the coordination to the patients' needs, individual situations and conditions. The contents of the manual include descriptions of the aims of the aftercare coordination, the processes of the study and the phone contacts and instructions for dealing with specific situations that are demonstrated via examples. The phone contacts should last 20 to 30 minutes each. After each phone contact, the therapists will complete a self-developed questionnaire that includes process documentation of the duration and contents of the contact (see process measurements).

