### Control condition

After inpatient treatment, the patients in the CG will receive treatment as usual with routine care that does not involve the aftercare coordination by phone that the patients in the intervention group will receive. The patients in the control group will not have any contact with their therapists from the clinic after the inpatient treatment.

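### Only the intervention arm is phoned by therapists, yet the stated 80% power assumes independent patients and the primary model names no therapist or unit effect

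*Protocol*

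**What the plan says.** All references are to the protocol.

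- **Delivery.** Under Intervention condition, IG patients receive six fortnightly calls "that will be performed by their inpatient treatment therapists for 12 weeks". The therapists are trained and have a manual, which "allows sufficient freedom to tailor the coordination" to the individual patient.
- **Control arm.** Under Control condition, these patients "will not have any contact with their therapists from the clinic after the inpatient treatment".
- **Sites and allocation.** Patients are recruited "in the four cooperating psychotherapeutic inpatient units". Under Randomization, "The randomization will take place at the individual level", with stratification by unit. The number of therapists is not stated.
- **Primary model.** Under Statistical analyses, "Comparisons between the IG and the CG will be calculated with mixed model analyses of covariance", "with symptom severity as the dependent variable and gender and initial symptom severity as covariates". The advantage given for the method is that it keeps persons who miss a time point. No therapist or unit effect is named.
- **Sample size.** Under Power calculation, the inputs are f = 0.25, about 30% less error variance from the baseline covariate, an adjusted f = 0.29, alpha 0.05, 80% power and about 50% dropout. They lead to N = 96 analysed and N = 192 enrolled. No caseload, ICC or design effect appears.

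**The concern.** With 96 IG patients planned from four units, each phoned by their own therapist, several IG patients will almost certainly share a therapist. If therapists differ in how well they conduct the calls, outcomes of IG patients with the same therapist are correlated. Control patients get no calls, so this correlation has no counterpart in their arm. The design is then partially nested: clustered in one arm and not in the other.

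An analysis that ignores this gives a standard error for the arm difference that is too small. A nominal 5% test then rejects too often under the null, and a test with the correct standard error has less power than the stated 80%. For the primary BDI-II comparison, this matters most if the p-value falls near 0.05.

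**Working it through.** **1. Reproduce the plan's figure.** Take a two-group ANCOVA with one covariate, independent patients and a 5% F test on 1 and N − 3 degrees of freedom, with noncentrality λ = N·f².

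- N = 96, f = 0.29: λ = 96 × 0.0841 = 8.07, power 80.3%.
- N = 94, f = 0.29: power 79.4%.
- Enrolment: 96 / (1 − 0.50) = 192.

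So N = 96 is what independence yields. It contains no allowance for clustering.

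**2. Check for slack.** The plan's own inputs give f = 0.25/√(1 − 0.30) = 0.299, not 0.29. With 0.299, N = 96 gives 82.6% power. The rounding down leaves a reserve of a little over 2 points.

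**3. Clustering in the IG only.** Let m be the analysed IG patients per therapist and ICC the within-therapist correlation of the outcome arising in the phone phase. Neither is in the protocol; both are assumed here.

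- Design effect in the IG: DE = 1 + (m − 1)·ICC.
- Variance of the arm difference relative to independence: k = (1 + DE)/2, as the control arm keeps DE = 1.
- Real type I error of the unadjusted test: 2·[1 − Φ(1.96/√k)].
- Power of a correct test: the F calculation of step 1 with f/√k.

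Worked case, m = 5 and ICC = 0.05: DE = 1 + 4 × 0.05 = 1.20; k = 2.20/2 = 1.10; √k = 1.049. Type I error is 2·[1 − Φ(1.869)] = 6.2%. The effective f is 0.29/1.049 = 0.276, which gives 76.5% power.

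**4. Range, 48 analysed per arm.**

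| m | Implied IG therapists (48/m) | ICC | k | SE factor √k | Type I error | Power, f = 0.29 | Power, f = 0.299 |
|---|---|---|---|---|---|---|---|
| 3 | 16 | 0.02 | 1.02 | 1.010 | 5.2% | 79.5% | 81.8% |
| 5 | about 10 | 0.02 | 1.04 | 1.020 | 5.5% | 78.7% | 81.1% |
| 4 | 12 | 0.05 | 1.075 | 1.037 | 5.9% | 77.4% | 79.8% |
| 5 | about 10 | 0.05 | 1.10 | 1.049 | 6.2% | 76.5% | 78.9% |
| 8 | 6 | 0.05 | 1.175 | 1.084 | 7.1% | 73.7% | 76.2% |
| 10 | about 5 | 0.10 | 1.45 | 1.204 | 10.4% | 64.6% | 67.2% |

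The power columns keep 93 error degrees of freedom. With few therapists the usable number is smaller, so they are slightly optimistic.

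**5. Therapist effects from the inpatient stay.** These are a different matter. Patients are randomised individually within unit, so a therapist's patients are spread over both arms. An effect of the inpatient treatment is shared by them and largely cancels in the arm difference. BDI-II at discharge, the baseline covariate, also absorbs part of it. Only the part that arises in the calls enters k.

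**The case against.** The strongest case on the other side has five parts.

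- **The model is not fully specified.** A reader might infer that the primary model contains no therapist effect. The protocol does not establish that. It says mixed model, lists fixed covariates and specifies no random effects at all, and a statistical analysis plan could add a therapist term. What stands is narrower: the section names none, and the reason it gives for the method concerns missing time points within a person. The sample size is not open in this way, because it is set in the protocol and rests on independence.
- **The large figures need unlikely inputs.** A reader might infer from the last row of the table that the type I error doubles. That row implies about five therapists across four units, although calls are made by each patient's own therapist and not by a small dedicated team. The documents do not support it as an expectation.
- **Little points to a high ICC.** The freedom to tailor is directed at patients' needs, which is variation between patients. Therapists are trained and use a detailed manual, and the endpoint lies six months after the calls end. This is fair: it argues for the lower ICCs, though not for zero.
- **There is slack.** With f = 0.299, power at m = 4 and ICC 0.05 is still 79.8%. So one cannot say that true power is below 80% over the whole plausible range.
- **Therapist effects cancel.** This holds for the inpatient part only. The phone-phase part cannot cancel, because one arm receives no calls.

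**Conclusion.** The point holds in a limited form. The design allows therapist correlation in the IG alone, the Statistical analyses section names no effect that would capture it, and the 80% under Power calculation assumes it is absent.

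Its size is unknown. For 3 to 5 analysed IG patients per therapist and an ICC of 0.02 to 0.05, the excess type I error is about 0.2 to 1.2 percentage points. Power is about 76% to 80% with the stated f, and 79% to 82% with the f that the plan's inputs give. At m = 8 and ICC 0.05 the figures are 7.1% and 74% to 76%. All of these rest on assumed caseloads and ICCs and on equal caseloads.

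The documents do not show that the trial is materially underpowered or its primary test badly miscalibrated. They show a dependence that the plan leaves unaddressed and that is cheap to handle.

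**What to change.** 1. **Data.** Record the treating inpatient therapist for every patient in both arms at recruitment. The therapists recruit the patients themselves, so the information is at hand. The call forms cannot serve as the source, because control patients have no calls.
2. **Statistical analyses.** Add the clinical unit, which is the randomisation stratum, as a fixed effect. Add a therapist-level random effect for the IG (partially nested), together with a therapist intercept shared by both arms if it can be estimated. Use Satterthwaite or Kenward-Roger degrees of freedom. State in advance that the model drops to the simpler random effect if the fuller one does not converge. Report the estimated ICC. Cluster-robust standard errors are a poor fallback: four units are too few, and the number of therapists may be too small as well.
3. **Power calculation.** State that 80% assumes no therapist clustering, give the expected number of therapists and caseload, and show power over a plausible range, as in the table above.

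The cost is one data field, a few sentences, a slightly wider confidence interval and a slightly less favourable stated power. No extra patients are needed for this change. It does not win back any power lost to clustering; it makes the loss visible and keeps the test near its nominal level.
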